## 4. INTRODUCTION

### 4.1. SEVERE ANAEMIA AND POST-DISCHARGE MORTALITY

Severe anaemia is a leading cause of hospital admissions in Africa contributing substantially to paediatric mortality. Our recent case-control study in Malawian children indicated that children aged <5y admitted with severe anaemia are not only at high risk of dying during the acute phase in-hospital (6%) but also for several months after they leave hospital: by 6 months post-discharge an additional 8% had died, which is nine times higher than the mortality rates in community-based, age matched children with mild anaemia. A further 8% were readmitted with rebound severe anaemia. Similar rates of post-discharge morbidity and mortality are seen in western Kenya, where 17.9% of children <5y admitted with severe anaemia died or were readmitted by 6 months ([name] et al, unpublished observations), while in Uganda as many as 36.5% died or were readmitted within 6 months ([name] et al, unpublished data). Hospitalised children with severe anaemia are particularly at risk within the first 3 months post-discharge, likely due to a combination of environmental, behavioural, nutritional and genetic risk factors.

### 4.2. MALARIA AS CAUSE OF POST-DISCHARGE SEVERE ANAEMIA AND MORTALITY

Because most deaths occurred at home the cause of death could not be assessed. However, previous observational studies in western Kenya and a recent intervention study in a high transmission area in Malawi showed that malaria in the post-discharge period is an important contributor responsible for a slow haematological recovery, rebound severe anaemia and morbidity. Many children in these areas experience episodes of new or recrudescing malaria infections after discharge which negates the initial rise in haemoglobin (Hb) achieved by blood transfusion in hospital. Haematological recovery from malaria-associated anaemia is known to take at least 6 weeks. This period may be prolonged in those with persistent or new malaria infections due to on-going red cell destruction and red blood cell production failure.

### 4.3. PREVENTION OF MALARIA POST-DISCHARGE AND HAEMATOLOGICAL RECOVERY

Standard treatment for severe anaemia in many countries in sub-Saharan Africa (SSA) consists of a blood transfusion, antibiotics if bacterial infections are suspected, and in the case of severe malarial anaemia, parenteral anti-malarial treatment (quinine or artesunate). Once children have stabilised and can be switched to oral treatment this is completed with short courses of 3-day treatment with artemisinin-based combination therapy (ACT), usually artemether-lumefantrine (AL). Children are often discharged with a short course of iron and folate, typically with no scheduled follow-up.

We hypothesize that by creating a prophylactic-time-window post transfusion, the bone marrow gets time to recover, resulting in a more sustained haematological recovery post-discharge. Data from Malawi show that this process takes 2-3 months in children with severe anaemia. The use of Intermittent Preventive Therapy (IPT) in children with 2 or 3 courses of artesunate plus

sulphadoxine-pyrimethamine, spaced monthly during the rainy season reduced clinical attacks of malaria by 86% in areas with highly seasonal transmission. IPT is the administration of a full treatment course of long-acting antimalarials at pre-defined time intervals irrespective of a patient's malaria status and clears existing infections and provides prolonged prophylaxis against new infections. The World Health Organisation's (WHO) recommended malaria control strategies include IPT for pregnant women (IPTp) and for infants (IPTi) and children (IPTc) living in areas with seasonal malaria transmission (now called seasonal malaria chemoprevention or SMC).

#### 4.4. IPT-PD TRIAL MALAWI 2013

We recently completed a multi-centre, randomized, placebo-controlled trial to determine the impact of malaria chemoprevention with Intermittent Preventive Therapy post-discharge (IPTpd) in 1441 children <5 years of age with severe anaemia in Malawi. This trial showed that provision of 3 months of chemoprevention with 3 full treatment courses of AL (which is eliminated slowly and provides several weeks of post-treatment prophylaxis), given in-hospital for initial malaria episode and at 1 and 2 months post-discharge, prevented 31% (95% CI 5-50, P=0.02) of deaths or readmissions due to severe anaemia or severe malaria (composite primary outcome) by 6 months post-discharge and 41% by 3 months (95% CI 10-62, P=0.014). The beneficial effect was in addition to the initial effect from the standard AL treatment course provided at discharge and in addition to any protective effect by insecticide treated nets (ITNs). These results are consistent with earlier findings from The Gambia, which showed that in children with severe anaemia, chemoprevention (as monthly IPT with SP or as weekly prophylaxis with pyrimethamine-dapsone) targeted during the malaria transmission season halved the rate of clinical malaria and reduced all-cause hospital readmission by 78% in one trial, and recurrence of severe anaemia by 78% in the other. These data are scarce, but indicate that IPTpd in the post-discharge period may potentially provide substantial health benefits.

#### 4.5. PROPOSED CONFIRMATORY TRIAL IN KENYA AND UGANDA

We propose to conduct a confirmatory efficacy trial in Kenya and Uganda to determine the efficacy and safety of 3 months of malaria chemoprevention post-discharge as an innovative potentially cost-effective strategy to reduce all-cause readmissions and deaths in children admitted with severe anaemia. We will call the intervention post-discharge malaria chemoprevention or PMC (instead of IPTpd), to illustrate the similarities with SMC rather than with IPTp in pregnancy. SMC and PMC malaria chemoprevention strategies aim to provide complete prophylaxis during a period of 3 to 4 months, whereas IPTp is given intermittently and allows for reinfections to occur between doses and provides partial protection.

### 5. JUSTIFICATION FOR THE STUDY

#### 5.1. WHY IS THIS STUDY NEEDED NOW?

In the past two decades, most research on severe anaemia and severe malaria focussed on reducing in-hospital mortality. Our observations suggest that a major, potentially preventable, component of the burden occurs after discharge and that a proactive approach using PMC could offer substantial public health gains. This is a priority area for research since no strategy specifically addresses this high-risk post-discharge period. The study sites include the two original sites that initiated post-

discharge risk research in the 1990s and hospitals in central and eastern Uganda that have identified a similar high post-discharge burden. These sites are representative for the main epidemiological settings appropriate for this intervention: i.e. moderate to high perennial transmission.

## 5.2. RATIONALE FOR ANOTHER PLACEBO CONTROLLED TRIAL

Although IPTpd / PMC represents a potential new strategy, it builds on existing strategies used for seasonal malaria chemo-prevention in West Africa and experience with IPT in pregnant women and infants. Policy makers and providers are familiar with the IPT and seasonal malaria chemoprevention concept and thus more likely to consider PMC if found to be effective and affordable. However there is no policy or strategy for post-discharge prevention in the countries where the studies are proposed and PMC is unlikely to be considered for policy by WHO or local Governments until these results from Malawi are confirmed in further placebo controlled trials in other countries and until more information is available on the potential delivery mechanism, its cost-effectiveness and potential impact. In addition, the impact on the disease burden and cost-effectiveness of PMC in the presence of other ongoing interventions (notably ITNs, and the recent switch from quinine for the treatment of severe malaria during the in-hospital period to the more effective in-hospital treatment with parenteral artesunate) will need to be assessed to provide the appropriate evidence base for National Malaria Control Programmes (NMCPs) to consider giving priority to this component by adding it to their national programmes rather than other potential focus areas. Furthermore, since the conduct of the original study with AL in Malawi, the long acting DP is now registered and available as second line treatment in both Kenya and Uganda as Duo-Cotecxin®, from Beijing HolleyCotec pharmaceutical Co. Ltd, China (henceforth referred to as HolleyCotec) DP is expected to be more effective than AL because it is longer acting providing approximately 4 weeks of near complete post-treatment prophylaxis. Previous studies in adults showed that when the 3-day courses are taken compliantly on a monthly basis it becomes prophylaxis and prevent almost all infections.

These different components will be addressed by a PMC Consortium funded by the Norwegian Government (see also section 12, page 62). This specific proposal describes the placebo controlled trial. A separate study of potential delivery mechanisms will be conducted in Malawi.

## 6. HYPOTHESIS

An additional three months of malaria chemoprevention with monthly 3-day treatment courses with DHA-piperaquine (each providing about 4 weeks of post-treatment prophylaxis) provided during the post-discharge period to children recently admitted with severe anaemia is superior to reduce all-cause readmission and mortality rates by 6 months compared with 2 weeks of post-treatment prophylaxis provided by the single course of oral artemether-lumefantrine when given as part of the standard in-hospital care around the time of discharge.

## 7. AIM AND OBJECTIVES

### 7.1. AIM

The study is designed to produce the necessary evidence required by WHO to review whether PMC should be recommended as a strategy for the post-discharge management of children with severe anaemia.

### 7.2. OBJECTIVES

#### 7.2.1. Primary objective

To determine if 3 months of post-discharge malaria chemoprevention with monthly 3-day treatment courses of dihydroartemisinin-piperaquine (DP) (PMC-DP) is safe and superior to the standard single 3-day treatment course with artemether-lumefantrine provided as part of standard in-hospital care in reducing all-cause readmissions and deaths by 6 months in the post-discharge management of children less than 5 years of age admitted with severe anaemia.

#### 7.2.2. Secondary objectives

To determine the cost-effectiveness of PMC-DP compared to current standard of care.

## 8. DESIGN AND METHODOLOGY

### 8.1. OVERVIEW STUDY DESIGN

This will be a multi-centre, parallel group, two-arm, placebo-controlled, individually randomized, superiority trial with 1:1 allocation ratio comparing the safety and efficacy of three courses of monthly PMC-DP or placebo post-discharge provided in addition to the standard single 3-day treatment course with artemether-lumefantrine provided as part of standard in-hospital care. Randomisation to PMC-DP or placebo will occur at 2 weeks after enrolment, and PMC-DP treatments will be administered at 2, 6 and 10 weeks. The primary outcome will be a composite of death or all-cause readmission between 2-26 weeks after enrolment. The study will be conducted in Uganda and Kenya, using randomisation stratified by age and study centre. The study will include a total of 1040 children (520 per study arm) less than 5 years of age who have been admitted for all-cause severe anaemia and have successfully completed the standard in-hospital treatment.

### 8.2. DESIGN CONSIDERATIONS

#### 8.2.1. Rationale for choice of DP for PMC

In order to provide complete prophylaxis for the entire 2-3 month duration that it takes for full hematologic recovery, the optimal regimen would consist of a drug which is sufficiently long acting to prevent the need to administer more often than monthly, as a regimen requiring more frequent administration is likely to result in lower compliance. Of the available antimalarials, SP, mefloquine, and DP have sufficiently long half-lives to be considered. There is high-grade resistance to SP in many parts of Africa and Asia, precluding its use for this purpose in malaria endemic areas in east

and southern Africa. Both piperazine (PQ) and mefloquine have long half-lives in children, thus providing approximately two weeks longer post-treatment prophylaxis (minimum of 28 days) than artemether-lumefantrine (minimum of 14 days) or amodiaquine-artesunate. Furthermore, in an evaluation of amodiaquine (alone, or combined with SP) for IPTp in Ghana, one of the amodiaquine arms was stopped prematurely because the drug was not well tolerated. Mefloquine is also not well tolerated and at treatment doses of 15 or 25 mg/kg is associated with frequent gastro-intestinal side effects, dizziness, and infrequently with serious neuro-psychiatric side effects, which is an important consideration when providing drugs for malaria prevention to asymptomatic and otherwise healthy children. Since DP is very effective, well tolerated, and provides 4 to 5 weeks of post-treatment prophylaxis, it is currently the superior candidate drug for IPTp and malaria chemoprevention.

### *8.2.2. Why in this study population?*

The primary study population involves children with all-cause severe anaemia, rather than children with severe malarial anaemia, which was the study population in the previous trial in Malawi. The rationale for this is that subsequent observational analysis in Uganda and western Kenya of data of post-discharge follow-up showed that children admitted with severe anaemia appear to be at increased risk of readmission and death regardless of whether they have evidence of malaria infection at the time of admission. Second, the differentiation between severe anaemia and severe malarial anaemia is not always feasible as it is common practice in many hospitals in sub-Saharan Africa to start parenteral treatment with antimalarials before the laboratory diagnosis of malaria is available. Furthermore the interpretation of malaria diagnostic tests on admission may be complicated in children with a history of recent antimalarial treatment in the days just prior to admission.

### *8.2.3. Efficacy vs effectiveness*

This is an efficacy trial, rather than an operational effectiveness study and each treatment course will be provided by study staff directly or by village based community health volunteers (CHVs) coordinated by study staff. As a minimum the first dose of each course will be observed. Where feasible, doses on day 2 and 3 will also be given under supervision, or compliance will be verified by home visits or contacting caretakers and/or CHVs by mobile phone.

### *8.2.4. Why this composite primary outcome?*

Use of clinical malaria as primary outcome would require a smaller study, however the composite severe outcome is used because it is more likely to drive policy. A composite outcome rather than a single severe outcome, such as death, is used to reduce sample size requirements.

### *8.2.5. Rationale for assessment by 6 months after enrolment*

The period 2-26 weeks, instead of 0-26 weeks is used for the primary efficacy analysis because children will only be randomized at 2 weeks. Prior to 2 weeks, all children, including those in the placebo arm, receive a 3-day course of AL as part of standard in-hospital care, which will be started while they are still admitted, and completed at home after discharge. The duration of post-treatment prophylaxis with AL is about 2 weeks, thus no differential effect is anticipated until children receive their first study specific intervention at 2 weeks post-discharge. A total of 26 weeks

(6 months) follow-up is included to capture whether the benefits achieved by 14 weeks (if any), when protective drug levels have waned in most children are sustained for a further 3 months.

#### *8.2.6. Rationale for testing of malaria and anaemia associated genes*

The study includes pheno/genotyping for the main polymorphisms that are known to provide protection against severe forms of malaria, including the haemoglobinopathies sickle cell trait/disease and thalassaemia, as well as G6PD deficiency, a hereditary enzyme deficiency. These are among the most common polymorphisms known. The carriers of these genes are partially protected from the adverse events associated with malaria, and are less likely to develop severe malaria illness, but some children may be more prone to develop chronic or severe anaemia. Unequal distribution by chance at randomisation of children with or without these genes could result in important bias of the study results (confounding). Similarly, the response to the treatment groups may differ between children with normal haemoglobin or normal enzyme-activity and children who carry the gene for haemoglobinopathies or G6PD deficiency. This can result in effect modification. These polymorphisms are common (>20%) and because the strength of the protective effect against severe malaria is considerable (70-90%), even small difference in distribution of these factors, or small modifications of the treatment effect, may have major implications on the observed effect. For a correct interpretation of the study results it is thus important to know the distribution of these polymorphisms between the study groups. For a description of the laboratory techniques see section 9.4.1, page 48.

#### *8.2.7. Rationale for testing parasite genetics and resistance-associate genes*

This study also includes genetic examination of the *Plasmodium falciparum* parasites infecting the enrolled patients. Parasite genetic material will be obtained from the same blood sample as those required for the clinical follow-up. Whole blood will be stored on filter paper blood spots for later processing. Genetic evaluation of the parasite can provide important insight into the degree of infection and importantly monitor for developing resistance due to ongoing drug pressure. First by examining the parasite genetic diversity, comparing baseline parasite composition to treatment and post-treatment complexity of infection (number of strains). The complexity of infection as well as the presence or absence of infection provides a gross measure for the efficacy of the PMC regimen in reducing the parasite burden. Second we will focus our genetic studies to monitor for signs of drug resistance. Artemisinin-based combination therapies have demonstrable parasite resistance in South East Asia and there is great concern that resistance will spread to or develop within Africa. Importantly we will monitor for signs that drug pressure is selecting for resistant parasite strains. Genes associated with parasite drug resistance will be sequenced including those implicated in artemisinin resistance (kelch K13), piperaquine (pvcrt), and lumefantrine (pfmdr1). Compared to baseline parasites we will determine if any mutations within these known drug resistance candidates have an increased frequency within the treated individuals. For a description of the laboratory techniques see section 9.4.1, page 48.

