## 8.5.2. Trial Medication and Interventions

### 8.5.2.1. PMC intervention schedule

Children will be randomised to one of the 2 treatment groups: Children in both arms will receive standard in-hospital care for severe (malarial) anaemia (blood transfusion, with or without antimalarial treatment with artesunate IV/IM). They will then all receive a 3-day course of artemether-lumefantrine (Coartem®, Novartis Pharmaceuticals) (AL) regardless of whether they were admitted with severe malarial anaemia or severe anaemia without evidence of malaria. At 2 weeks post-discharge, surviving children will be randomized to receive a standard 3-day course of DP at 2, 6, and 10 weeks post-discharge or an identical placebo regimen (Table 1, page 14). If children receive AL for malaria during any unscheduled out-patient visit or during a readmissions, the PMC schedule will be adapted accordingly such that any next course of DP is given at least 2 weeks after the start of the last course of AL; e.g. if a child was due to receive the 2nd course of DP at 6 weeks post-discharge, but is treated for malaria with AL during an unscheduled visit at 5 weeks, then the 6-week course of DP (or placebo) is provided in week 7 instead of week 6, and the subsequent course in week 11 instead of week 10.

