#### 8.7.5. Visit 4: Randomisation and 1st PMC treatment visit

Randomisation will take place during visit 4, 2 weeks post enrolment, by opening a single concealed envelope containing the study drugs which will be pre-packed by the study pharmacist (for full details about the randomisation and blinding, see section 8.10, ‘Assignment of interventions and blinding’, page 42. The first PMC treatment visit can take place at home or in the clinic, subject to local circumstances. The first dose of medication will be observed, and the family will be given the study drug to administer at home on the subsequent 2 days. Prior to drug administration, a finger prick will be taken for Hb determination and a filter paper blood spot for parasite genetics.

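### Section 8.2.7 judges parasite resistance markers and complexity of infection against baseline in treated children without the placebo arm, so a change cannot be attributed to DP

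*Protocol*

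**What the plan says.** Section 8.2.7 describes two uses of the parasite genetic data. The first concerns the number of strains per infection: "comparing baseline parasite composition to treatment and post-treatment complexity of infection (number of strains"). It adds: "The complexity of infection as well as the presence or absence of infection provides a gross measure for the efficacy of the PMC regimen". The second concerns resistance, using genes "implicated in artemisinin resistance (kelch K13), piperaquine (pvcrt), and lumefantrine (pfmdr1"). The comparison for these is "Compared to baseline parasites we will determine if any mutations within these known drug resistance candidates have an increased frequency within the treated individuals". The placebo arm is not mentioned in either.

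No other section supplies an arm comparison for parasite genetics. Section 8.6 lists no parasite-genetic outcome, section 9.2 has no analysis of it, and section 9.4.1 covers laboratory technique only.

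On treatment, section 8.2.5 says: "Prior to 2 weeks, all children, including those in the placebo arm, receive a 3-day course of AL as part of standard in-hospital care". Section 8.5.2.1 gives that course to every child "regardless of whether they were admitted with severe malarial anaemia or severe anaemia without evidence of malaria". Malaria during follow-up is treated with AL again (Table 1), and section 8.5.2.1 provides for this: "If children receive AL for malaria during any unscheduled out-patient visit or during a readmissions, the PMC schedule will be adapted accordingly".

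Parasite samples are planned at enrolment (8.7.3.5), at the randomisation visit (8.7.5: "Prior to drug administration, a finger prick will be taken for Hb determination and a filter paper blood spot for parasite genetics"), at unscheduled visits for malaria (8.7.8.1) and at six months (8.7.7). None is restricted to one arm.

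**The concern.** The purpose given in 8.2.7 is to watch for selection of resistant strains under drug pressure and to gauge how well PMC reduces parasite burden. A comparison with baseline in treated children is uncontrolled. It combines any effect of DP with the effects of AL, recovery from the acute illness, new infections, season and calendar time. AL matters especially because the panel includes the gene that the protocol ties to lumefantrine, AL's partner drug, and the gene it ties to artemisinins, a class present in both AL and DP.

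A rise in marker frequency could therefore be read as selection by DP when it has another cause, or real selection could be masked by an opposing trend. A fall in complexity that occurs in both arms could be read as a PMC effect. The trial is meant to supply evidence for a WHO recommendation (section 7.1), and resistance selection is one of the questions such a review would ask. A placebo arm sampled on the same schedule is available and unused in the stated comparison.

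**Working it through.** **Step 1: what lies between baseline and follow-up.** The protocol states no figure here, so there is none to reproduce.

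| Source of change | DP arm | Placebo arm | Section |
|---|---|---|---|
| AL course before the first study dose | yes | yes | 8.2.5, 8.5.2.1 |
| AL for malaria during follow-up | possible | possible | Table 1, 8.5.2.1 |
| Up to six months of time, season and new infections | yes | yes | 8.7.1, 8.3 |
| DP | yes | no | 8.5.2.1 |

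A before-after comparison in the DP arm reflects all four rows. A same-time comparison between arms removes what the first and third rows have in common. It does not fully remove the second, because DP should change how often rescue AL is needed.

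Some children have taken part of their AL before enrolment (8.5.2.2), so part of that exposure can precede the enrolment sample. Parenteral artesunate is normally complete before enrolment screening (8.7.3.1) and is not counted here as an exposure after baseline.

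**Step 2: illustration of size.** Every input is an assumption: n1 = 300 baseline infections; n2 = 30, 60 or 100 follow-up infections in the DP arm; baseline marker prevalence p = 10, 30 or 50%; a shift d = 5, 10 or 20 points, equal in both arms; no DP effect; independent samples; two-sided 5% test.

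The chance that the before-after test declares an increase is

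Φ[(d − 1.96·SE0)/SE1], with

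SE0 = √{p̄(1−p̄)(1/n1+1/n2)} and SE1 = √{p(1−p)/n1 + (p+d)(1−p−d)/n2},

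where p̄ is the pooled prevalence.

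Example with p = 30%, d = 10 points, n2 = 60:
- p̄ = (90 + 24)/360 = 0.317
- SE0 = √(0.317 × 0.683 × 0.02) = 0.0658
- SE1 = √(0.21/300 + 0.24/60) = 0.0686
- (0.10 − 1.96 × 0.0658)/0.0686 = −0.42, so the chance is 34%

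Results for n2 = 30 / 60 / 100:

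| Baseline prevalence | Shift 5 points | Shift 10 points | Shift 20 points |
|---|---|---|---|
| 10% | 17 / 23 / 29% | 41 / 58 / 72% | 82 / 96 / 99% |
| 30% | 9 / 12 / 16% | 22 / 34 / 46% | 61 / 84 / 95% |
| 50% | 7 / 10 / 14% | 18 / 29 / 41% | 56 / 83 / 95% |

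The ranges are 7–29%, 18–72% and 56–99%. Under the same assumptions the two arms have equal expected prevalence at follow-up, so a concurrent comparison stays near the nominal 5%.

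**Step 3: which sample is baseline.** Section 8.2.7 does not say. Section 8.7.3.5 calls the enrolment samples baseline measurements. The baseline block of Table 2 marks both enrolment and the randomisation visit. Section 9.2.2 uses everything collected before randomisation, and section 9.6.1 uses the term for the ECG before the first DP dose. If the week-2 spot is meant, the initial AL course no longer lies between the two samples. Later AL, season and time still do.

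**The case against.** The strongest reply is that 8.2.7 is a rationale paragraph, not an analysis section. Parasite genetics is neither an objective nor a listed outcome, and section 9.2 says that a later SAP will supersede the protocol. Sampling in both arms leaves an arm comparison open. That is right about status and is why the point is limited. It does not remove the point: the paragraph names its comparison and that comparison is uncontrolled, so this is a method stated badly rather than a detail deferred.

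Four stronger readings are tempting and are not supported:

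- **That selection by AL will be reported as selection by PMC-DP.** The text speaks of drug pressure without naming PMC, and its inclusion of a lumefantrine marker fits monitoring under all the trial antimalarials. What stands is that the stated comparison could not tell the sources apart.
- **That the fall in complexity from baseline is itself declared to be the efficacy measure.** The sentence names complexity together with presence or absence of infection. Infection at six months is already a listed secondary outcome (8.6.3) and open to arm comparison.
- **That each child is compared with its own admission sample.** The text states neither pairing within child nor which sample is baseline. The weakness is the same if the comparison is unpaired.
- **That comparing infected children between arms is a fully protected randomised contrast.** It conditions on infection after randomisation, which DP affects, and on rescue AL use, which will probably differ between arms.

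The AL argument is also weaker for the piperaquine marker, for which time, season and new infections are the main alternative explanations.

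**Conclusion.** The point holds in limited form. As worded, 8.2.7 would judge marker frequency and complexity by an uncontrolled change in treated children, and such a change cannot be attributed to DP. This rests on the stated comparison, the AL given to every child, the possibility of further AL and the length of follow-up.

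The size is unknown. The false-positive range of 7 to 99% across the scenarios depends wholly on assumed prevalences, sample counts and shifts, and shows only that a modest common shift is enough to mislead. The analysis is exploratory, and nothing here touches the primary endpoint or the listed infection outcome. It is worth correcting, but it is no threat to the trial's main conclusion.

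**What to change.** Amend 8.2.7 as follows.

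1. Make DP versus placebo, as randomised and at matched post-randomisation times (malaria episodes and month 6), the main comparison for marker frequency and complexity.
2. Report carriage of each marker, and complexity, per randomised child, counting uninfected children as not carrying the marker. This measures the burden of resistant parasites and will fall if DP prevents infection, so a lower figure does not by itself rule out selection.
3. Report marker prevalence among infected children by arm as a supporting analysis, with a note that it conditions on post-randomisation infection and on differing rescue AL use.
4. State which sample is baseline. Give changes from the enrolment sample and from the pre-dose week-2 sample by arm, as descriptive only, since few children may be parasitaemic at week 2.

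The cost is text and analysis: samples from both arms are already planned, and section 9.4.1 expects most of the sequencing towards the end of field work. The drawback is limited precision, because there will be few infections in the DP arm. The comparison with baseline has the same limit.
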